**Objective:**

This study aimed to introduce a protocol that tests the independent and interactive effects of EFT and PosA on TD, food choice, and food demand in overweight and obese adults.

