### This Study

This protocol aims to test whether an intervention focused on enhancing both the reward value of healthy foods and regulation surrounding unhealthy foods is likely to have a stronger effect on eating behavior compared with interventions focused on either process alone. To achieve this, we will conduct a 2×2 factorial, randomized, controlled lab-based intervention study of brief guided imagery exercises that target regulation (EFT: yes, no) and reward (PosA imagery: positive, neutral) mechanisms of eating behavior.

To assess the individual and combined effects of EFT and PosA on eating behavior, we will examine the effect of PosA, EFT, and their interaction on (1) TD, (2) the reward value of healthy and unhealthy foods (ie, food demand indexed by intensity or the number of items consumed when freely available), and (3) food choice. Our predictions are 3-fold. First, we predict that participants in the EFT condition will demonstrate lower TD, lower demand for unhealthy foods, higher demand for healthy foods, more healthy food choices, and less unhealthy food choices compared with the ERT condition. Second, we predict that participants in the PosA condition will demonstrate no differences in TD, yet exhibit lower demand for unhealthy foods, higher demand for healthy foods, more healthy food choices, and less unhealthy food choices compared with the neutral affect conditions. Third, we predict that participants in the EFT and PosA conditions will demonstrate the lowest TD, the lowest demand for unhealthy foods, the highest demand for healthy foods, the healthiest food choices, and the least unhealthy food choices compared with participants in all other conditions.

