### Sample Size

The target sample size of 156 participants (39 participants per group) is based on 2 prior studies testing EFT interventions. Sze et al [22] found that Web-based training in EFT (vs ERT) reduced TD with an effect size of *η*^2^=0.18. O’Neill et al [23] found that smartphone-delivered training in future (vs recent) episodic thinking impacted food choice by reducing total calorie consumption (*η*^2^=0.28) and percent calories consumed from fat (*η*^2^=0.28). We plan to use a mixed-design analysis of variance (ANOVA) with treatment arm (4 arms) as the between-subject variable and measurement period (baseline, after allocation, and closeout) as the within-subjects variable. As the EFT cue utilized by O’Neill et al was personalized to each participant and was delivered repeatedly via smartphone, and this protocol includes none of those design features (the intervention content is standardized and delivered once), we predict a smaller effect size. To be conservative, we predict the interaction between time and intervention arm variables will yield a standardized effect size of 0.17. Attrition rates commonly observed in brief guided imagery intervention studies are approximately 20% [32,33]. Therefore, we aim to recruit 156 total participants (39 participants per group) to allow for an analytic total sample of 124 participants with 31 participants in each group. This would provide 95% power to detect a statistically significant interaction between intervention arm and measurement period at the .05 level while adjusting for attrition.

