### Intervention Content

Initial scripts for the interventions were developed and then presented to an advisory panel of professionals who are experts in guided mental imagery stimuli, affect manipulation, future episodic thinking, and eating from the United Kingdom and United States. Guided imagery scripts were also presented to 2 face-to-face community advisory panels, one in the United States and the other in the United Kingdom. The intervention development process is described in detail elsewhere [39].

During the guided imagery including PosA (arm 1 [PosA-EFT intervention] and arm 2 [PosA intervention]), participants will be invited to think of positive feelings and associations surrounding healthy fruits and vegetables. They will be asked to imagine themselves appreciating the healthy food and to bring awareness to the positive aspects of the food, such as its color, feel, smell, taste, and health benefits. Additionally, participants in the PosA-EFT intervention (arm 1) will then be invited to think in detail of a future where they have made healthy food choices. The EFT intervention (arm 3) focuses on future-oriented thinking as described above, but includes no positive emotions surrounding healthy food. Finally, the ERT intervention control (arm 4) asks participants to think about a recent event and aims to rule out potential effects of guided imagery alone on food decision-making and TD and to control for the effort involved in imagining an event at a different time than the present. The interventions will be delivered during the first experimental session (see the Experimental Sessions section below) using Qualtrics survey software to play the audio recording of the guided imagery for each of the 4 intervention arms.

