### Analysis

#### Primary Statistical Analysis

Our primary statistical analyses will comprise a mixed design (between-subjects and repeated measure) that compares TD, food demand, and food choice measures at baseline, after allocation, and at closeout across treatment arms. Our analyses will control for standard demographic variables such as age, biological sex, race, and income. A series of repeated measure ANOVAs with treatment arm as a between-subject variable and measurement period as the repeated measure will be conducted on TD rates and healthy and unhealthy food demand indices, respectively.

In addition, to examine the effect of the intervention arms on food choices inside and outside the lab, a series of ANOVAs will be conducted on healthy and unhealthy snack food choices and average daily serving intake values for each of the food categories. To probe the effect of the intervention on in-lab food choices, we will conduct a repeated measure ANOVA with measurement period repeated across treatment group on health and unhealthy snack food choices. Next, to probe the effect of the intervention on food choices outside the lab, we will conduct a 1-way ANOVA with treatment arm entered as the between-subject variable on average daily serving intake values for the primary food categories (ie, fruit and vegetable intake).

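### The questions are factorial, but the only test stated and powered is a four-arm by period omnibus test that cannot by itself separate EFT, PosA and their interaction

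*Protocol article*

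**What the plan says.** The Objective in the abstract is a protocol that "tests the independent and interactive effects of EFT and PosA on TD, food choice, and food demand in overweight and obese adults". The section This Study repeats this ("we will examine the effect of PosA, EFT, and their interaction on (1) TD") and makes three predictions:

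1. EFT differs from the recent-thinking (ERT) condition on temporal discounting (TD), food demand and food choice.
2. PosA differs from neutral affect on demand and choice, while "participants in the PosA condition will demonstrate no differences in TD".
3. The combination gives the lowest TD and the best demand profile, together with "the healthiest food choices, and the least unhealthy food choices compared with participants in all other conditions".

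The same section frames the aim as whether targeting both processes "is likely to have a stronger effect on eating behavior compared with interventions focused on either process alone". The Discussion adds a prediction of synergy.

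The analysis is described differently. Sample Size: "We plan to use a mixed-design analysis of variance (ANOVA) with treatment arm (4 arms) as the between-subject variable", crossed with three measurement periods; the 95% power is claimed for the arm by period interaction. Primary Statistical Analysis: "A series of repeated measure ANOVAs with treatment arm as a between-subject variable and measurement period as the repeated measure will be conducted". Food choice is handled with the same arm coding, and intake outside the lab with a one-way ANOVA on arm. Nowhere are EFT and PosA entered as separate factors, an EFT × PosA term named, or a contrast between particular arms prespecified.

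On the control content, Intervention Content says: "Finally, the ERT intervention control (arm 4) asks participants to think about a recent event". Study Design attaches ERT to arm 4 only, and Table 1 lists arm 2 as positive affect alone.

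**The concern.** An arm by period F test on 6 df is one question: do the four arms have the same profile over time? Rejecting it is compatible with an EFT effect alone, a PosA effect alone, both added together, or a response confined to the combined arm. None of the three predictions follows from it. Prediction 2 on TD needs an estimate specific to PosA, and prediction 3 needs arm 1 compared with each other arm.

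Two things are at stake. Contrasts picked after seeing the arm means would be post hoc, in a trial with several primary outcomes. And a reader may take the 95% as the power for the synergy hypothesis, which it is not.

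A related matter is what the 2×2 contrasts would estimate. If recent thinking occurs only in arm 4, the two arms without EFT are not alike: one has PosA imagery without ERT, the other has ERT. An effect of the ERT recording would then enter the interaction.

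**Working it through.** **Inputs from Sample Size:** effect 0.17 for time by arm (metric not named; read here as Cohen's f), 124 analysed (31 per arm), k = 4 arms, m = 3 periods, alpha 0.05, stated power 95%, attrition about 20%. **Assumed, not in the document:** correlation ρ between repeated measures of 0.5 (range shown) and sphericity.

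**Step 1. Reproduce the stated power.**
- λ = f²·N·m/(1−ρ) = 0.17² × 124 × 3 / 0.5 = 21.50.
- df = (k−1)(m−1) = 6 and (N−k)(m−1) = 240.
- Power from the noncentral F is 0.951, and 124 is the smallest N that reaches 0.95. For attrition, 124/0.8 = 155, against 156 planned (4 × 39).

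So the 95% is reproduced, and it belongs to the 6-df omnibus test. It depends on ρ: 0.84 at ρ = 0.3 and 0.998 at ρ = 0.7.

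**Step 2. Split the 6 df.** With equal arms, arm by period divides into EFT × period, PosA × period and EFT × PosA × period, 2 df each. The share of λ that a term receives is (p·c)²/(p·p), where p holds the centred arm means and c is the unit contrast; for the interaction c = (1, −1, −1, 1)/2.

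Example: only the combined arm responds. The means (1, 0, 0, 0) centre to (3/4, −1/4, −1/4, −1/4), so p·p = 3/4. For the interaction p·c = 1/2, and the share is (1/4)/(3/4) = 1/3. EFT and PosA also receive 1/3 each. Per term, λ = 21.50/3 = 7.17.

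**Step 3. Power with the omnibus effect held fixed (ρ = 0.5).**

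| Pattern of response | Omnibus, 6 df | EFT × period | PosA × period | EFT × PosA × period |
|---|---|---|---|---|
| EFT only | 0.951 | 0.99 | 0.05 | 0.05 |
| PosA only | 0.951 | 0.05 | 0.99 | 0.05 |
| Both, additive | 0.951 | 0.84 | 0.84 | 0.05 |
| Combined arm only | 0.951 | 0.66 | 0.66 | 0.66 |

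Entries of 0.05 are the false-positive rate where the true effect is nil. In the last row the factorial terms have power 0.51 at ρ = 0.3 and 0.88 at ρ = 0.7. The omnibus column does not change, so the omnibus result cannot tell these rows apart.

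For prediction 3, arm 1 versus arm 2 and arm 1 versus arm 3 (each by period, 2 df) have power 0.53 each if effects are additive and 0.93 each if only the combined arm responds.

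**Step 4. The ERT content.** Let P and E be additive effects and R the effect of the ERT recording, with ERT in arm 4 only. Arm means are P+E, P, E and R.
- Interaction: (P+E) − P − E + R = R.
- Pooled EFT: ½[(P+E−P) + (E−R)] = E − R/2.
- Pooled PosA: ½[(P+E−E) + (P−R)] = P − R/2.

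With no true synergy, the interaction equals R, and both pooled effects are shifted by −R/2. The document gives no value for R.

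**The case against.** A four-level arm factor and a 2×2 coding fit the same four cell means, so every factorial effect is a contrast within the stated ANOVA. The article calls the design 2×2 and says the interaction will be examined; the contrasts may stand in an analysis plan that is not shown. This is also a pilot. Much of this stands. A reader might infer that the planned analysis cannot address the aims at all. The documents do not support that: what is absent is the statement of the contrasts, not the capacity to compute them. But the article does state the model, in two sections, and sizes the trial on its omnibus test, so the mismatch lies in what is written and is not simply detail left out.

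A reader might also infer that the 6-df test costs a great deal of power for an EFT effect. At an assumed 0.4 SD (ρ = 0.5) it would be 0.43 against 0.62 for the 2-df term, but that effect size is not the protocol's. An EFT effect of d at both later periods gives f = d/√18, so the protocol's 0.17 corresponds to d = 0.72, where the figures are 0.951 and 0.990. Nor does the article say that the omnibus F decides the hypotheses or gates further tests.

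Finally, the absence of ERT from arm 2 is well indicated by Study Design, Intervention Content and Table 1, but is not said outright. Step 4 is therefore conditional, and recoding the model does not remove the problem.

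**Conclusion.** The concern holds as a mismatch between stated questions and stated test. The questions concern EFT, PosA, their interaction and the combined arm against all others; the only test specified and powered is arm by period on 6 df, which alone cannot separate them. The 95% is arithmetically sound for that omnibus test, but it does not carry over to the interaction, which has about 66% power if only the combined arm responds (51% to 88% for ρ from 0.3 to 0.7). A single term carrying the whole effect would have 99%. These figures rest on 0.17 being Cohen's f, on sphericity, on the assumed ρ and on the response pattern, and they apply to the outcomes measured at three periods. If ERT is confined to arm 4, an interaction cannot be read as synergy without allowing for R.

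**What to change.** - **Primary Statistical Analysis:** replace the arm term with EFT, PosA and EFT × PosA, each by period. Use the same three terms without period in place of the one-way ANOVA on intake outside the lab.
- **Contrasts:** prespecify arm 1 versus arm 2, versus arm 3 and versus arm 4, all three required for prediction 3. Name arm 3 versus arm 4 as the EFT-versus-ERT contrast.
- **Sample Size:** say that the 95% applies to the omnibus arm by period test, name the effect-size metric and the assumed correlation, and give power for the factorial terms over a range of correlations.
- **Interpretation:** state whether arm 2 contains any recent-thinking segment. If it does not, state that the interaction includes any ERT effect R and that the pooled EFT and pooled PosA effects are each shifted by −R/2.

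The cost is rewording and a short power table. The drawback is a less favourable stated power for the interaction. Design, data collection and sample size do not change.

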**Assessments**									
	Baseline: TD^b^	—	X	—	—	—	—	—	—
	Baseline: Food demand	—	X	—	—	—	—	—	—
	Outcome: TD	—	X	—	—	—	—	—	X
	Outcome: Food demand	—	X	—	—	—	—	—	X
	Outcome: Food choice	—	X	—	—	—	—	—	X
	Outcome: Daily food surveys	—		X	X	X	X	X	—
	Assessments before allocation^c^	—	X	—	—	—	—	—	—
	Assessments after allocation^d^	—	X	—	—	—	—	—	—
	Assessments at close out^e^	—		—	—	—	—	—	X
	Repeated assessments (before allocation and at close out)^f^	—	X	—	—	—	—	—	X

^a^—: not applicable.

^b^TD: temporal discounting.

^c^Assessments before allocation: food frequency, reward-based eating, health-specific self-efficacy, weight related eating, health locus of control, perceived stress reactivity.

^d^Assessments after allocation: emotion regulation, trait mindfulness, behavioral motivations, impulsiveness, mental health history, physical health history, demographics.

^e^Assessments at closeout: global self-reported health, self-reported weight status, social desirability, coping responses, tobacco and alcohol use, sleep quality, loneliness, psychological flexibility.

^f^Repeated assessments (before allocation and at closeout): stages of change in weight management; *Covariate measures included in analyses*: perceived stress, positive and negative affect, and depressive symptoms.”

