### Primary Outcome Measures

#### Temporal Discounting

The minute monetary TD task will be given at baseline, after allocation, and at closeout to assess TD. During the minute monetary TD task, participants answer 5 questions about their preference to receive specific monetary rewards over time (now vs later). Across consecutive trials, participants are presented with a fixed set of choices between smaller, immediate rewards and larger, delayed rewards (US $1000 in 3 weeks or US $500 now) with the temporal distance being adjusted at each trial (now, 4 days, 1 week, 3 months, and 2 years). The 5 questions are taken from a list of 64-item pairs with differential money and time options. The questions adjust based on the participants’ prior response to identify their delay discounting rate. For example, the participants select which option they would rather have “US $500 now” or “US $1000 in 3 weeks.” If the “US $1000 in 3 weeks” is selected, the next question will feature the same monetary reward at a more distant time (ie, “US $1000 in 1 year”). However, if the “US $500 now” option is selected, the next question will feature the US $1000 reward at a more proximal time (ie, “US $500 now” or “US $1000 in 1 day”). In this way, the reward amount or time will be titrated to identify the rate (ie, k-value) at which the participant discounts monetary rewards over time. The TD rate will be calculated for each participant and then compared across treatment group as a between-subjects variable and as a within-subjects repeated measure variable, comparing the effect of the treatment (baseline compared with after allocation and at closeout).

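### Temporal discounting and food demand would be compared more precisely with baseline as a covariate than as a third outcome level, and the diary model could use the pre-allocation food frequency measure

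*Protocol article*

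**What the plan says.** **TD and food demand.** The Sample Size section plans a mixed-design ANOVA with "treatment arm (4 arms) as the between-subject variable and measurement period (baseline, after allocation, and closeout) as the within-subjects variable". The Temporal Discounting section has the same structure: the TD rate is compared across groups and also as a "within-subjects repeated measure variable, comparing the effect of the treatment (baseline compared with after allocation and at closeout". The Food Demand section treats demand intensity, its primary index, in the same way, and Primary Statistical Analysis confirms repeated-measures ANOVAs of arm by period. Under Experimental Sessions, the baseline TD and demand tasks come before the intervention.

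**Diary.** For fruit and vegetable intake outside the lab, Primary Statistical Analysis says "we will conduct a 1-way ANOVA with treatment arm entered as the between-subject variable on average daily serving intake values". Footnote c of Table 1 shows that a dietary measure is taken earlier: "Assessments before allocation: food frequency, reward-based eating, health-specific self-efficacy".

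**Covariates.** Primary Statistical Analysis lists demographic variables. Footnote f of Table 1 adds perceived stress, affect and depressive symptoms. Neither list contains a baseline outcome value or baseline diet.

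**The concern.** A value measured before randomisation cannot carry a treatment effect. Its use is to explain differences between people that would otherwise sit in the error term. As a level of the response, baseline enters the comparison with a fixed weight: the contrast of later visits with baseline is in effect a change score, which subtracts the whole baseline value whether or not it predicts the later one that well. A covariate lets the data choose the weight.

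The between-group comparison also named in the Temporal Discounting section averages over all three periods. An effect sustained at both later visits would therefore appear there at two-thirds of its size.

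For the diary, people differ in what they habitually eat. A model with arm alone leaves all of that in the error term. With about 31 analysed per arm, wider intervals than necessary are a real cost.

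**Working it through.** **1. Reproducing the stated power.** Inputs from Sample Size:
- effect: "we predict the interaction between time and intervention arm variables will yield a standardized effect size of 0.17"; the metric is not named, and it is read here as Cohen's f;
- numbers: "analytic total sample of 124 participants with 31 participants in each group";
- claim: "This would provide 95% power to detect a statistically significant interaction between intervention arm and measurement period at the .05 level".

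The correlation between visits is not given, so rho = 0.5 is assumed. For the within-between interaction with m = 3 periods:

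lambda = N f² m/(1 − rho) = 124 × 0.0289 × 3/0.5 = 21.50, with df (4 − 1)(3 − 1) = 6 and (124 − 4)(3 − 1) = 240.

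Power is 0.951 (0.948 by simulation). The stated 95% reproduces. It depends on rho: 0.84 at rho = 0.3 and 0.998 at rho = 0.7.

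**2. TD and demand: variance of the arm contrast.** Assume equal variances (set to 1) and a common correlation rho among the three visits.
- Mean of the two post values minus baseline: (1 + rho)/2 + 1 − 2 rho = 3(1 − rho)/2.
- Mean of the two post values adjusted for baseline: (1 + rho)/2 − rho² = (1 − rho)(1 + 2 rho)/2.
- Ratio: (1 + 2 rho)/3.

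| rho (assumed) | Change-type | Adjusted | Ratio |
|---|---|---|---|
| 0.3 | 1.05 | 0.56 | 0.53 |
| 0.5 | 0.75 | 0.50 | 0.67 |
| 0.7 | 0.45 | 0.36 | 0.80 |
| 0.8 | 0.30 | 0.26 | 0.87 |

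For a single post value the variances are 2(1 − rho) and 1 − rho², so the ratio is (1 + rho)/2: 0.75 at rho = 0.5 and 0.85 at rho = 0.7.

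**3. What this means for power on the plan's own inputs.** Read f = 0.17 as a shift sustained at both post-allocation visits. The pattern (0, 1, 1) has variance 2/9 over three periods, so the between-arm variance of the shift is 0.0289 × 9/2 = 0.130. At N = 124 and rho = 0.5:
- planned interaction, 6 df: lambda 21.50, power 0.951;
- change-type contrast, 3 df: lambda 124 × 0.130/0.75 = 21.50, power 0.980;
- baseline-adjusted contrast, 3 df: lambda 124 × 0.130/0.50 = 32.25, power 0.999.

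The first step, 0.951 to 0.980, comes only from the narrower test. The gain due to baseline adjustment is 0.980 to 0.999.

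**4. Diary.** With a covariate correlated r with the outcome, residual variance is multiplied by 1 − r².

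| r (assumed) | Variance factor | Reduction | Equivalent N (124/factor) |
|---|---|---|---|
| 0.2 | 0.96 | 4% | 129 |
| 0.4 | 0.84 | 16% | 148 |
| 0.5 | 0.75 | 25% | 165 |

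These ratios leave the demographic covariates aside. Where those are also fitted, r should be read as the correlation that remains after them.

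**The case against.** The strongest reply is that this is a choice between valid models. The arm-by-period test is sound under randomisation, it does use baseline, and the Sample Size, outcome and analysis sections agree on it. That stands, but it does not remove the efficiency loss.

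Several stronger readings should be resisted.
- A reader might infer that the planned analysis is biased or invalid. Nothing in the protocol supports this. Chance imbalance is already reflected in the error term.
- A reader might infer that the trial is underpowered or its power statement wrong. The 95% reproduces with the planned test, at an assumed rho of 0.5.
- A reader might take the whole interaction for a change-from-baseline test. With three periods, its 6 degrees of freedom also cover after-allocation against closeout.
- A reader might say that the diary's baseline is ignored. The diary is kept only after allocation, so it has no baseline on the same instrument. The food frequency measure is a proxy, and its items, units and recall period are not in the article.
- A reader might call the diary comparison wholly unadjusted. The sentence on demographic control precedes all the models and may cover it. Baseline diet is absent either way.

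It can also be objected that the ratios assume equal variances. Their size does. The direction does not: the fitted slope minimises residual variance, so a fixed weight of 1 can at best match it, apart from the degree of freedom spent.

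**Conclusion.** The point holds as a matter of efficiency. For TD and for healthy and unhealthy demand intensity, treating baseline as an outcome level gives a valid test that is less precise than baseline adjustment. On the mean of the two post values the saving in variance runs from 47% at rho = 0.3 to 13% at rho = 0.8, and is one third at rho = 0.5, the value at which the protocol's power figure reproduces. On the planning effect, power is already high, so the practical benefit is narrower intervals and more room if the true effect is smaller than planned.

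For the diary the conclusion is weaker, because it depends on how well an instrument that is not shown predicts diary intake. The gain could be as small as 4% at r = 0.2.

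All these sizes rest on assumed correlations. The change is worth making because the data are already being collected, not because the present analysis would mislead.

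**What to change.** - **TD and healthy and unhealthy demand intensity:** model the after-allocation and closeout values with arm, period and their interaction, taking the participant's baseline value as a covariate. Equivalently, keep all three visits in a mixed model and constrain the baseline means to be equal across arms. Retain the stated demographic covariates.
- **Diary fruit and vegetable intake:** replace the arm-only 1-way ANOVA with an ANCOVA that adds the pre-allocation food frequency measure, using its fruit and vegetable items if the instrument contains them, together with the stated demographics.

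The cost is a change of analysis wording and one degree of freedom per covariate. No new data are needed, and the sample size and power statement can stand. The Results section reports 84 of 156 participants completed at submission with recruitment still open, so the change could be fixed in writing before the final analysis.
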